**Program B fortification program time: approximately 21 minutes.**		
**Cool down**		
[figure not shown]	**1 minute**	Antero-posterior and latero-lateral walk.
[figure not shown]	**30 seconds on each side**	Active stretching of the gluteus maximus.
[figure not shown]	**30 seconds on each side**	Active stretching of the quadriceps.
[figure not shown]	**30 seconds on each side**	Active stretching of the hamstring.
[figure not shown]	**30 seconds on each side**	Active stretching of the gastrocnemius.
[figure not shown]	**2 minutes**	Immersion in the whirlpool.
**Total cool down time: approximately 8 minutes.**		

In program C (high-intensity protocol), the same sequence of exercises stipulated for program B will be respected, however, the quantity of work will be modified based on the variables time and speed of the performance of the movement.
^
47
^ Fortification activities will be performed for 6 minutes, and the speed must be adjusted in order to stimulate the performance of the movement for the subjective sensation compatible with the Borg’s zone of interest 15 (hard) to 18 (very hard). In the same way, walking activity will be replaced by running activity which amounts to an approximate time of 39 minutes.

The reference group will be submitted to the same aquatic physiotherapy protocols, however, only the biochemical parameters and the self-perception questionnaires will be evaluated.

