## Methods

### Trial design

This is an interventional transversal study, randomized clinical trial, crossover type with three arms: low, medium, and high-intensity aquatic physiotherapy.

This clinical intervention protocol follows the recommendation from the Standard Protocol Items: Recommendations for Interventional Trials (SPIRIT).
^
31
^
^,^
^
32
^ The study sample, defined according to criteria, will be submitted to a single session of each one of the following modalities of aquatic physiotherapy: (a) low-intensity, (b) medium-intensity, and (c) high-intensity. Among each modality, a minimum of a 15-day wash-out period will be respected, in accordance with
Figure 1.

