**Figure 1. f1:**
[figure not shown]
Flow of interventions and assessment parameters.

For this study, 15 participants will be recruited. The sample size calculation indicated a non-centrality parameter (δ) of 3.8, suggesting a moderate effect on biomarker variations. The critical t-value was 2.10, with degrees of freedom (df) of 16.143, resulting in a total sample size of 15 participants and an actual power of 0.95. The effect size calculation was based on means and standard deviations, and for our main dependent variables, these were reported by previous investigations: Germanou
^
33
^ through the antioxidant levels and Nascimento
^
34
^ through the MMP-2 and MMP-9 analysis between the control and intervention group, in this case, it is represented by patients with knee osteoarthritis.

The assessment parameters used in each variable will consist of instruments that allow for the assessment of the variations in the MMP-3 concentration, oxidative stress, pain, edema, and flexibility. In addition, a self-perception questionnaire, developed by the authors, will be applied to assess self-perception. It consists of a Likert scale where the patient must classify their perception of well-being between zero and 10, where zero represents the worst feeling of well-being and 10 represents the best feeling of well-being. The data collection form, informed consent form and patient identification form can be found as
*Extended data.*
^
32
^ The trial has been registered on
ClinicalTrials.gov (
NCT05610696, 18/01/2023).

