### Eligibility criteria

The following eligibility criteria will be considered: being over 50 years old and diagnosed with osteoarthritis in at least one knee according to the American College of Rheumatology
^
35
^ criteria, referring to pain and at least one dysfunction for at least six months, absence of physical limitation that prevents the performance of the exercises protocol, have Kellgren and Lawrence classification between III and IV
^
36
^ and independent gait. Subjects who present autoimmune inflammatory conditions, use of psychotropic, immunosuppressant, or steroids drugs, consumption of antioxidants (vitamin E, statins, or uric acid reducers), alcohol and tobacco, progressive ankylosis states, the coexistence of neurological lesions, infections or skin diseases that contraindicate swimming pool immersion, surgical procedures on the knee joint in the last 12 months (excluding meniscectomy or arthroscopy), lower limb articular prosthesis, presence of inflammatory or infectious disease, uncontrolled systemic arterial hypertension, uncontrolled diabetes, chronic obstructive pulmonary disease and history of ischemic heart disease, self-reported aquatic phobia, and chlorine allergy will be excluded from the study. For control purposes, a reference group will be constituted with age matching and exclusion criteria identical to the experimental group.

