### Outcomes

Initially, all participants will be interviewed and evaluated in relation to the degree of osteoarthritis and functionality. Information regarding the patient data will be confirmed
*via* interview, considering data such as complete name, date of birth, age, affected knee(s), duration of pain, arterial blood pressure, list of medications in use, consumption of tobacco or alcohol, associated diseases, if they are undergoing physiotherapy treatment or regular physical activity.

The classification regarding the degree of osteoarthritis will be performed by analyzing the radiograph of the affected knee according to the method of Kellgren and Lawrence. The radiographs will be analyzed, the degree of osteoarthritis will be identified with the negatoscope support, and the images in the digital form will be displayed on a computer screen, considering the classification expressed in degrees ranging from zero to IV.

Subsequently, the identification of functionality will be assessed according to the Brazilian version of the Knee Injury and Osteoarthritis Outcome Score (KOOS). The KOOS questionnaire was developed in the 1990s as an instrument to evaluate the patient’s perception of their knee and associated problems. Since its first publication in 1998, the psychometric properties of KOOS were evaluated in a systemic review of 37 articles demonstrating adequate validity in its use for the study population.
^
37
^

Regarding the pre- and post-intervention assessment instruments, all participants will have the following parameters evaluated: concentration of MMP-3 and GPx, pain, edema, flexibility, and self-perception of the general well-being. In addition, it should be noted that in the 24-hour-follow-up, only the biochemical concentrations and the self-perception questionnaire will be reevaluated.

The biochemical variables will be measured in peripheral blood from the concentrations of MMP-3 and GPx. The levels of MMPs will be measured based on the Enzyme-Linked Immunosorbent Assay (ELISA) methodology, which is based on the antigen-antibody interaction and will be performed according to the kit manufacturer’s instructions. MMP-3, a constituent of the stromelysin family that is an important mediator responsible for the degradation of collagen type II, IX, and XI,
^
12
^
^,^
^
13

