**Fifteen seconds rest between each exercise** **Total program time: approximately 45 minutes**		

As a starting position to perform the exercises, the participants must remain in the semi-flexion position of their knees so that the water line must remain at shoulder height throughout the procedure. All the exercises will be performed according to the established time, and a 15-second rest time will be added between each exercise or series. As a manner of manipulating the intensity of the exercise at low intensity, the movement speed will be standardized according to the subjective sensation of effort according to Borg 6-20,
^
44
^ with zones of interest from 6 (extremely light) to 9 (very light). In this intervention modality, we will seek to understand the impact that the physiological effects of immersion in heated water pose on the studied variables.

Program B will consist of a sequence of exercises adapted from previous works
^
45
^
^,^
^
46
^ composed of warm-up, fortification, and cool-down activities. Aquatic steppes platforms will be used to ensure that all participants, when performing the exercises in orthostatism, will maintain the waterline level approximately at the level of the xiphoid appendix. For this program, the exercises will be performed at a speed that guarantees a comfortable water level for the activity, being the effort zones of interest from 10 (fairly light) to 14 (somewhat hard).

The warm-up sequence consists of four different active moves performed at maximum movement amplitude and contributes to neuromuscular activation.

After the warm-up, the participants will be submitted to the fortification program, which consists of a sequence of seven exercises aiming to promote muscular activation. The participants will be encouraged to perform the movement at a comfortable speed with the maximum possible movement amplitude. During sitting exercises, the need to maintain the lumbar spine in a neutral position will be emphasized in order to avoid overloading this segment.

To finish program B, as a way to calm down, a sequence of three activities will be performed, including a period in the hydromassage area, according to
Table 2.

**Table 2. T2:** Program B: medium-intensity protocol. The individuals in the images are students of the Physiotherapy course who consented and authorized their image.

Warm-up		
Exercise	Periodization	Description
[figure not shown]	**4 minutes**	Antero-posterior and latero-lateral walk.

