### Statistical analysis

The resulting data will be tabulated, considering the absolute values and their respective standards. Information regarding the main outcome corresponding to the variations in the concentrations of MMP-3 and GPx in peripheral blood due to three different aquatic physiotherapy interventions will be comparatively evaluated among the distinct interventions and among the different times (in pre- and post-intervention moments).

The information on the outcome regarding pain, edema, and flexibility will be comparatively assessed among the different types of intervention. Statistical analyses will be performed in the SPSS software and will be considered as a significance level when p>0.05 through the repeated measures ANOVA statistical test.

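### No session-free comparison exists, so the pre-post change in MMP-3 and GPx cannot be attributed to the sessions; the reference group does the same programs and does not supply one

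*Protocol article*

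**What the plan says.** - **Design.** Trial design describes a "crossover type with three arms: low, medium, and high-intensity aquatic physiotherapy". Each participant has one session of each program, with a washout between them. No period or arm is free of a session.
- **Purpose of the reference group.** Eligibility criteria: "For control purposes, a reference group will be constituted with age matching and exclusion criteria identical to the experimental group".
- **What that group does.** The end of Interventions: "The reference group will be submitted to the same aquatic physiotherapy protocols". For this group "only the biochemical parameters and the self-perception questionnaires will be evaluated". The Abstract says the same, so this is not a slip.
- **Sampling.** Outcomes places T0 just before the session, T1 just after it and T2 at 24 hours. Every sample is tied to a session.
- **Analysis.** Statistical analysis gives the variations in MMP-3 and GPx as the main outcome and describes them as due to the three interventions. They are to be compared between the interventions and also "among the different times (in pre- and post-intervention moments", by repeated measures ANOVA.
- **Program A.** Interventions says that in this program "we will seek to understand the impact that the physiological effects of immersion in heated water pose on the studied variables".

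**The concern.** A change from T0 to T1 or T2 can be credited to a session only if the same change without a session is known or can safely be taken as zero. This design never observes the markers over that interval without a session. The group labelled as a control might be expected to fill the gap, but its members do the same programs and pass through the same sampling times.

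The immersion aim for Program A has the same difficulty. All three programs are done in the pool and both groups do them, so no contrast in the trial sets immersion against no immersion.

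At stake is the wording of the main result. If the time comparison is significant, the plan as written invites the conclusion that aquatic physiotherapy changed MMP-3 or GPx, and the design cannot identify that.

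**Working it through.** **The plan's own figure.** The sample-size paragraph in Trial design gives non-centrality 3.8, critical t 2.10, df 16.143 and power 0.95. A two-sided 5% noncentral t calculation with df 16.143 gives critical t 2.118 and power 0.946, so the stated power reproduces. It concerns the chance of detecting an effect. It says nothing about whether a detected time effect comes from the session.

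**What each comparison can identify.** Write the mean change from T0 in program p as (session effect of p) + (drift), where drift is whatever would have happened between the samplings without a session.

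| Comparison | What it estimates | Drift removed? |
|---|---|---|
| Change over time, all programs pooled | average session effect + drift | No |
| Change over time within one program | that program's effect + drift | No |
| Program A change read as immersion | immersion + exercise + drift | No |
| Reference group versus patients, same program | difference between the groups in (effect + drift) | Only if drift is equal in both; the session effect itself is not recovered |
| Program versus program, change from T0 | difference between two session effects | Yes, if drift is common to all sessions |

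Only the last row isolates a contrast between programs, and it is randomised within person because the order of programs is randomised (Assignment of interventions).

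**Size of the problem for the time test.**

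Inputs from the article: n = 15 and 3 sessions per person. The 5% level is taken as two-sided.

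Assumed, because the documents give no figure: the drift d, in SDs of the change from T0 in one session; the correlation r between one person's session changes; no true session effect. The test is simplified to a single T0-to-T1 contrast averaged over the three sessions.

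- Variance of a person's mean change over 3 sessions = SD² × (1 + 2r)/3.
- Standard error over 15 people = SD × √[(1 + 2r)/45].
- Non-centrality = d × √[45/(1 + 2r)], with df = 14 and critical t = 2.145.

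For d = 0.3 and r = 0: 0.3 × √45 = 2.01, which gives 47%. For d = 0.3 and r = 1: 0.3 × √15 = 1.16, which gives 19%.

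| Drift d | r = 0 | r = 0.5 | r = 1 |
|---|---|---|---|
| 0 | 5% | 5% | 5% |
| 0.2 | 24% | 14% | 11% |
| 0.3 | 47% | 26% | 19% |
| 0.5 | 88% | 60% | 44% |

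The entries are the chance of a significant time effect when the sessions do nothing. The column r = 1 equals a paired test on one session. The error rate is 5% only when drift is zero.

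**The case against.** **The trial is mainly a comparison of intensities.** Statistical analysis names the comparison between interventions first, and a repeated measures ANOVA over programs and times can contain the program-by-time term. This stands. A reader might infer that the trial as a whole lacks a valid comparison; it does not, because the between-program contrast is randomised within person. Only the time comparison and the immersion statement are exposed.

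**The reference group may never have been meant as an untreated control.** Its matching covers age and exclusion criteria only, and pain, edema and flexibility are not measured in it. That fits a comparator for disease status, and giving such a group the same sessions would then be sensible. This is plausible but not stated. Even so, the group could show only whether the response differs between groups, and the article's wording of its purpose suggests more.

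**Stronger readings that the article does not support.**
- *Immersion confounds the session effect.* Immersion is part of aquatic physiotherapy. What lies outside the session is time of day, repeated sampling and similar drift.
- *The sample size promises a control-versus-treatment test that the analysis omits.* The phrase "analysis between the control and intervention group" describes the earlier studies that supplied the effect size, not a planned comparison.
- *Outcomes contradicts Interventions on what is measured.* Outcomes says "all participants will have the following parameters evaluated", and Interventions then makes an explicit exception for the reference group.
- *The reference group's size and its comparison are missing, so its data go unused.* A condensed article commonly leaves such detail to the full protocol or analysis plan.
- *Bias has been shown.* It has not. No document gives the size or direction of any drift.

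An unseen analysis plan could add a group comparison. It could not supply a session-free interval, so the core point does not depend on what that plan contains.

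**Conclusion.** The point holds for the marginal time effect and for the immersion attribution, and no further. The main outcome includes a pre-post comparison whose result is described as due to the interventions. The design has nothing that separates that change from non-session drift, and the reference group cannot do so because it does the same programs.

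With n = 15, 3 sessions and a two-sided 5% test, a drift of 0.3 SD gives a false positive in 19% to 47% of trials and one of 0.5 SD in 44% to 88%. Each range runs from a within-person correlation of session changes of 1 down to 0. These figures rest on assumed drifts, and the top of each range needs independent session changes within a person. They show how sensitive the time test is, not that drift is present. The conclusion is that the pre-post effect is not identifiable; the difference between programs in change from T0 remains sound under a drift common to all sessions.

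**What to change.** 1. In Statistical analysis, state that claims about effects on MMP-3 and GPx rest on the program-by-time contrast, that is, the difference between programs in change from T0.
2. Report pre-post changes within each program with confidence intervals, labelled as descriptive, and do not describe them as due to the intervention.
3. In the Program A text, remove the statement that it will show the impact of immersion.
4. In Eligibility criteria, replace the control wording for the reference group with a statement that it can show only whether the response differs between groups, not whether the session caused the change.

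This changes wording only; no visit, sample or participant is added, and the article gives the study status as not yet recruiting. The cost is that pre-post p-values no longer support an effect claim, so the trial will speak to differences between intensities and not to the effect of a session against none.

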### Recruitment

The population will be recruited from the physiotherapy services of Universities. The study will also be disseminated in print and digital media, social networks of the researcher, the university, the academic directory of health courses, the Medical Leagues and institutional pages.

### Assignment of interventions

*Allocation:* Participants will be allocated randomly to establish the sequence within each group, following a computer-generated randomization schedule from
randomize.com, as exemplified by the flowchart in
Figure 1.

*Blinding:* This study is classified as single-blinded, indicating that the researchers responsible for conducting the assessment instruments and laboratory analysis procedures will be distinct from those administering the intervention protocols.

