^ will be considered for this analysis. Oxidative stress will be measured by analyzing the peripheral blood from percutaneous punction. The sample collection time will be performed according to the study by Nascimento
^
34
^ and will be in accordance with the following times: T0 (immediately before the intervention), T1 (immediately after the intervention), and T2 (24 hours after the intervention).

The assessment of the degree of pain will be performed using the visual analogue pain scale,
^
38
^ from a scale graduated from zero to 10, in which zero corresponds to cases without pain and 10 corresponds to the worst imaginable pain.

The assessment of edema will be performed based on the measurement of the circumference of the affected knee(s). The measure will be performed with the patient relaxed in dorsal decubitus and the circumference will be determined with the knee in extension, based on the proximal distance of 1 cm from the base of the patella.
^
39
^ For that, the same measuring tape will be used for all measurements.

The flexibility will be assessed by measuring the amplitude of the active and passive movement for the knee flexion and, for that, a conventional goniometer will be used. The goniometer will be used because it has a low cost, is easy to handle, allows the assessments to be performed quickly, and the measurements and movement amplitude for the knee joint are valid and reliable.
^
40
^ For the assessment, the knee will be free of clothing, and the patient will be positioned in dorsal decubitus with the hip articulation at 90° of flexion. The fixed arm of the goniometer will be positioned parallel to the thigh with an orientation towards the greater trochanter of the femur and the mobile arm will be parallel to the lateral face of the fibula, directed towards the lateral malleolus. The movement reading will be performed while maintaining the final possible position of the arc of movement where the highest reading degree represents the assessed measurement.
^
41
^ All procedures will be performed by a single physiotherapist.

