### Data collection, management, and analysis

*Data collection methods:* The interviews, evaluation of radiological images, application of instruments and measurements of pain, edema, and flexibility will be carried out only by a single qualified, trained physiotherapist, with familiarity with the instruments and with adequate training. Blood sample collection will be performed by a nursing professional familiar with this procedure. Laboratory analyzes will be performed by another researcher qualified biomedical pharmacist. The application of the intervention protocols will be carried out by two physiotherapists trained in aquatic physiotherapy and who will not participate in the interviews, radiological analysis and evaluation of edema, pain and flexibility.

*Data management:* All data will be entered electronically
*via* Microsoft Excel. The study’s digital forms will be inserted and received in a cloud file with access only to the researcher. Participant files will be stored in numerical order and stored in storage for a period of 3 years after completion of the study. Modifications to data recorded in the database will be documented through the data breach system associated with your user identification code and password. Access to study data will be restricted. All reports will be prepared in such a way that no subject can be identified.

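### Single-blinding is explained only as separation of staff, which can be met without anyone being masked to the program

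*Protocol article*

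**What the plan says.** Under Assignment of interventions, the blinding paragraph calls the study single-blinded and gives the meaning of the term in the same sentence: the "researchers responsible for conducting the assessment instruments and laboratory analysis procedures will be distinct from those administering the intervention protocols".

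The division of roles is repeated under Data collection, management, and analysis. Interviews, radiograph reading and the measurements of pain, edema and flexibility are "carried out only by a single qualified, trained physiotherapist". A nursing professional draws blood. For the assays: "Laboratory analyzes will be performed by another researcher qualified biomedical pharmacist". The two physiotherapists who deliver the programs are people "who will not participate in the interviews, radiological analysis and evaluation of edema, pain and flexibility".

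Under Outcomes, edema is a tape measurement of knee circumference. For active and passive knee flexion, "a conventional goniometer will be used". That section adds: "All procedures will be performed by a single physiotherapist". Pain (a 0 to 10 visual analogue scale) and well-being (0 to 10) are rated by the participant. The abstract places pain, edema and flexibility before and immediately after the intervention. Statistical analysis names the changes in MMP-3 and GPx as the main outcome and compares pain, edema and flexibility between the types of intervention.

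**The concern.** A separate assessor is someone who does not deliver the treatment. A masked assessor is someone who does not know which treatment was delivered. The article offers the first as the meaning of a label that readers will take as the second. The trial could follow its definition to the letter, report itself as single-blinded, and still have had an assessor or analyst who knew the program.

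This matters most where the observer produces the number. Tape and goniometer readings involve judgement about tape position and tension, arm alignment and the end of the movement. One person takes all of them, so no second reader can dilute an expectation. If that person knows the program and expects more swelling or less movement after the high-intensity session, the expectation enters the comparison between programs. The crossover removes stable differences between participants. It does not remove a reading error that changes with the program.

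**Working it through.** **1. What the definition requires, set against what masking requires.**

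| Role | What the article states | Stated to be unaware of the program? |
|---|---|---|
| Clinical assessor (one physiotherapist) | Different person from the therapists | No |
| Laboratory analyst (biomedical pharmacist) | Different person from the therapists | No |
| Nurse drawing blood | Familiar with the procedure | No |
| Two treating physiotherapists | Do not assess | Not possible |
| Participant | Undergoes all three programs | Not possible, and not claimed |

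The sections on trial design, outcomes, interventions, assignment, data collection, analysis, monitoring and ethics contain no statement that anyone is kept unaware of the program or sequence. They mention no withheld sequence list, no coded tubes and no request to participants not to describe the session.

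**2. Which outcomes are exposed.**

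- Knee circumference and goniometry are read by one observer before and immediately after each session. This is the greatest exposure.
- MMP-3 (ELISA, following the kit instructions) and GPx are the main outcome and are laboratory measurements. The exposure is smaller but not nil, since nothing is said about sample labels.
- Pain and well-being are rated by participants who know what they have just done. Masking the assessor cannot change this.

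**3. Whether the assessor could infer the program.** The target effort is Borg 6 to 9 in program A, 10 to 14 in B and 15 to 18 in C, and the clinical readings follow immediately. Without precautions the program could be learned or guessed. Even with them, visible exertion after C may give it away.

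**4. An illustrative size.** The plan has no figure to reproduce here: it gives neither a measurement error nor a reading bias. Both inputs below are assumptions. Take a paired comparison of two programs with N = 15, so df = 14 and the two-sided 5% critical value is 2.145. Suppose there is no true difference but a systematic reading bias b between the programs, and let SD be the standard deviation of the within-person difference in flexion. Then

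noncentrality = b / (SD / √15),

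and the false-positive rate is the probability that a noncentral t with 14 df falls outside ±2.145.

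For SD 6 the standard error is 6/√15 = 1.549. For SD 10 it is 10/√15 = 2.582.

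| Assumed bias (degrees) | SD 6: noncentrality | SD 6: rate | SD 10: noncentrality | SD 10: rate |
|---|---|---|---|---|
| 1 | 1/1.549 = 0.645 | about 9% | 1/2.582 = 0.387 | about 7% |
| 2 | 2/1.549 = 1.291 | 23% | 2/2.582 = 0.775 | 11% |
| 3 | 3/1.549 = 1.936 | 44% | 3/2.582 = 1.162 | 19% |

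The article plans a repeated measures ANOVA over three programs, so the paired test is a simplification. The table shows how sensitive a comparison of 15 people is to a small systematic reading error. It does not estimate the bias in this trial.

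**The case against.** The strongest reply is that silence about procedure does not prove that the procedure is absent. A reader might infer from the definition that nobody in this trial is masked. The documents do not support that: they never say that the assessor or analyst knows the program. Separate staff are compatible with masking and usually a precondition for it, and the label itself suggests that masking of these two roles was intended. This part of the reply stands.

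It can also be said that custody of the sequence list, tube labels and instructions to participants are details that a journal article leaves to the full protocol. That is fair for the details taken one by one. It does not rescue the definition, because the article does not leave the term open: it says what the label means, and what it says is not masking.

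Three further limits stand. The observer-read outcomes are not the main outcome, which rests on blood assays run by a separate person. Self-reports by unmasked participants are unavoidable with exercise programs, and no participant blinding is claimed, so this is not a defect. The false-positive rates depend wholly on the assumed bias and SD, and with a bias of 1 degree they stay near the nominal level, at about 7% to 9%.

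**Conclusion.** The point holds as a fault in the stated definition. The article equates single-blinding with separation of staff, and that definition can be satisfied without the protection the label implies. Whether the assessor and analyst will in fact be masked cannot be determined from the text.

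The consequence falls mainly on knee circumference and range of motion, less on MMP-3 and GPx, and it does not alter the open-label nature of pain and well-being. No size can be derived from the documents. The range of about 7% to 44% is purely illustrative and rests on an assumed bias of 1 to 3 degrees, an assumed SD of 6 to 10 degrees, 15 complete pairs and a paired t test. The point should be settled before recruitment, which the article says has not begun, because masking cannot be added after the readings are taken.

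**What to change.** Rewrite the blinding paragraph so that single-blinded means that the clinical assessor and the laboratory analyst are masked to program and sequence, and say how:

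- The sequence list is withheld from both.
- The assessor stays out of the pool area, and participants are asked not to describe the session.
- Tubes carry codes that show neither program nor time point, and the code is kept closed until the assays are complete.
- The text states that participants and therapists are not masked, so pain and well-being are open-label self-reports.
- The text acknowledges that visible exertion after the high-intensity program may partly unmask the assessor.

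If masking will not be done, drop the single-blinded label and describe the trial as having assessors and laboratory staff separate from the therapists.

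The cost is a revised paragraph, coded labels and control over who holds the list. No extra staff are needed, because the roles are already separate. The protection will be least secure for comparisons with the high-intensity program, for the reason given in the last bullet.
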